## 9.2 Endpoints

9.2.1 Primary Endpoint

Population- and subject-specific first-phase plasma HIV-1 RNA level decay rates d1 (as estimated from biexponential decay models fit to plasma HIV-1 RNA level data through day 56).

9.2.2 Secondary Endpoints

9.2.2.1 Population- and subject-specific first-phase plasma HIV-1 RNA level decay rates d1 (as estimated from biexponential decay models fit to plasma HIV-1 RNA level data through day 56).

9.2.2.2 Population- and subject-specific second-phase viral load decay rates d2 (as estimated from biexponential decay models fit to viral load data through day 56); population- and subject-specific third-phase decay rates d3 as estimated from plasma HIV-1 RNA levels obtained during weeks 24 to 72.

9.2.2.3 Proportion of subjects with viral load <50 copies/mL 24, 48, and 72 weeks after initiation of RAL and FTC/TDF. If the first detectable viral load corresponds to the sample collected at the last visit, the subject will be counted as detectable (at this visit) without confirmation.

9.2.2.4 Safety and Tolerability

- Incidence of Grade 3 and 4 symptoms and laboratory results by body system and by type, excluding asymptomatic elevations in lipids or CK.
- Incidence of permanent discontinuation of study medication for any reason.
- Incidence of permanent discontinuation of study medication for reasons other than virologic failure.
  - - 1. Change in CD4+ T-cell count from baseline to weeks 24, 48, and 72. The baseline CD4+T-cell count will be the arithmetic mean of the two measurements obtained on different days closest before or on the day of study medication dispensation (e.g., pre-entry and entry determinations). If only one such measurement is available, then this measurement will be the baseline value.
      2. RAL-, FTC- and TDF-resistance mutations using very sensitive resistance assay measures in subjects with detectable viremia.
      3. Subject-specific estimates of: (a) the minimum concentration (Cmin) for RAL, FTC, and TDF; (b) viral load changes on day 7; (c) CD4+ T-cell counts changes over days 0-14 (magnitude of changes and estimated slope). The baseline HIV-1 RNA will be the geometric mean of the two measurements obtained on different days closest before or on the day of study medication dispensation (e.g., pre-entry and entry determinations). If only one such measurement is available, then this measurement will be the baseline value.
      4. Adherence by self-report at each study visit.
      5. Total cell-associated proviral DNA, LTR circular DNA, and integrated proviral DNA as measured by an assay currently undergoing validation; and unintegrated linear proviral DNA calculated by subtraction, measured on days 0, 2, 7, 10, 14, 21, 28, and 56; weeks 12, 24, 48, and 72; and at the time of virologic failure.
      6. Plasma HIV-1 RNA levels collected from week 24 through week 72, as quantified by the single copy assay. If enough points are above the lower limit of the single-copy assay, the rate of change over the third (and possibly fourth) phase of viral decay will be estimated.
      7. CD4+ T-cell counts measured on days 0, 2, 7, 10, and 14.
      8. Subject-specific estimates of first-phase viral decay rate; CD4+ T-cell restoration (changes from baseline in CD4+ T-cell count) as measured at days 7, 14, 28, 56, weeks 24, 48, and the final visit; counts of CD4+ and CD8+ T-cell subsets that are (a) naïve (CD45RA+/CD27+), (b) CM (CD45RA-/CD27+), and (c) effector memory (CD45RA-/CD27-); and of each of these, counts that are in cell cycle (Ki-67+) and/or activated (express one or both of the activation markers CD38 and HLA-DR).

## 9.3 Randomization

For this single-arm study, randomization is not necessary.

## 9.4 Sample Size and Accrual

A total of 34 subjects will be accrued. Assuming subject enrollment from at least 7 sites, and a rate of 2 subjects every 3 months at each site, accrual is expected to be completed within 7.5 months.

The primary objective of the study is to estimate the first-phase viral decay rate in treatment-naïve subjects receiving RAL and FTC/TDF. As was done in ACTG viral dynamics substudies A5160s (parent study A5142) and A5166s (parent study A5095), plasma HIV-1 RNA levels will be measured at pre-entry and entry (geometric mean of these to be used as baseline) and as per the Schedule of Events. Plasma HIV-1 RNA measurements through day 56 will be used in estimating the first and second phase viral decay constants d1 and d2. Measurements obtained after treatment interruptions and/or rebound will be excluded. A parametric nonlinear mixed effects model for bi-exponential decay will be fit to the remaining on-treatment data, yielding subject-specific empirical Bayes estimates (EBEs) of d1 and d2. Ninety-five percent CIs around the subject-specific estimates will be reported.

Estimates of d1 obtained for subjects on ACTG A5166s and A5160 are shown in Table 6. For both studies, the difference in d1 between the arms with the best and poorest outcomes (highest and lowest d1; also lowest and highest rates of virologic failure in the parent study) was 0.11. For the three treatment groups in A5166s, population mean estimates (± standard deviations), derived from the estimated covariance matrix on the parameter estimates arising from the Markov chain Monte Carlo (MCMC) approach, ranged from 0.58±0.06/day to 0.70±0.18/day. An alternate derivation, from the 25th and 75th percentiles around the EBEs reported in Table 2 of the manuscript, and using the rule of thumb that the interquartile range is approximately equal to 1.35 times the standard deviation,(43) yields somewhat smaller estimates of 0.10 and 0.12, respectively.[[1]](#footnote-2) When the same back-calculations are applied to the EBEs for d1 reported in the final analysis report for A5160s, standard deviations (SDs) of d1 are estimated as 0.09, 0.18 and 0.09 for arms A, B and C, respectively. Móltó et al. reported d1 estimates of 0.80 and 0.62 for their 5- and 4-drug regimens, respectively (a difference of 0.18 between arms); SDs around these estimates were given as 0.13 and 0.18, respectively.(44)

For various combinations of sample size and SD of d1 estimates, Table 7 presents the resulting “plus-minus” amounts (half-widths) of 95% CIs. For example, if the population SD of d1 is 0.20, a sample size of 30 subjects (with usable data) will provide CI lower and upper bounds ± 0.07 around the mean. If the true SD(d1) is smaller than 0.20, CIs will be narrower. Assuming the population mean d1 for the study regimen is 0.80, Table 8 presents the probability that 95% CIs will lie entirely above the value 0.65. For example, if the population mean and SD of d1 are 0.80 and 0.20, respectively, and the sample size is 30 subjects with usable data, there is 98% probability that the 95% CI around the sample mean will exclude (and fall above) the value d1=0.65.

Approximately 14% of subjects who enrolled to A5166s had to be excluded from analysis due to drug interruptions. (HIV-1 RNA levels excluded for non-monotonicity were a subset of these.) To allow for such losses in the current study, a buffer of 4 additional subjects is added to the goal of 30 analysis-eligible subjects, bringing the accrual target to 34.

Table 6. Estimates of d1 and its standard deviation from similarly designed and analyzed viral dynamics studies.

| Study | Arm | Estimated  d1 | Estimated  SD(d1) |
| --- | --- | --- | --- |
| A5166s (A5095) | C: EFV + 3TC/ZDV (superior arm) | *0.67  **0.70 | *0.10  **0.18 |
|  | B: ABC + 3TC/ZDV | *0.56  **0.58 | *0.12  **0.06 |
|  | A: EFV + ABC + 3TC/ZDV | 0.59 | 0.08 |
| A5160s (A5142) | C: EFV + 2 NRTIs (superior arm) | 0.64 | 0.09 |
|  | A: EFV + LPV/r | 0.61 | 0.09 |
|  | B: LPV/r + 2 NRTIs | 0.53 | 0.18 |
| Móltó | ENF + EFV + LPV/r + 3TC + TDF | 0.80 | 0.13 |
|  | EFV + LPV/r + 3TC + TDF | 0.62 | 0.18 |

* From subject-specific estimates. ** From MCMC-based population estimates.

Table 7. Expected precision for d1 estimates for various combinations of sample size and underlying population standard deviations around true d1. Precision expressed as ± amounts (half-widths) for 95% CIs (assuming normality of d1).

| Sample size | Population standard deviation around d1 | | | | | |
| --- | --- | --- | --- | --- | --- | --- |
| 0.12 | 0.15 | 0.18 | 0.20 | 0.23 | 0.25 |
| 10 | 0.09 | 0.11 | 0.13 | 0.14 | 0.16 | 0.17 |
| 15 | 0.07 | 0.08 | 0.10 | 0.11 | 0.13 | 0.14 |
| 20 | 0.06 | 0.07 | 0.08 | 0.09 | 0.11 | 0.12 |
| 25 | 0.05 | 0.06 | 0.07 | 0.08 | 0.09 | 0.10 |
| 30 | 0.04 | 0.06 | 0.07 | 0.07 | 0.09 | 0.09 |

Table 8. Probability that the 95% CI around the estimated d1 will lie entirely above the value 0.65, assuming the population mean d1 is 0.80.

| Sample size | Population standard deviation around d1 | | | | | |
| --- | --- | --- | --- | --- | --- | --- |
| 0.12 | 0.15 | 0.18 | 0.20 | 0.23 | 0.25 |
| 10 | 94% | 80% | 65% | 56% | 45% | 40% |
| 15 | 99% | 95% | 85% | 77% | 65% | 58% |
| 20 | 100% | 99% | 94% | 89% | 79% | 72% |
| 25 | 100% | 100% | 98% | 95% | 88% | 82% |
| 30 | 100% | 100% | 99% | 98% | 93% | 89% |

## 9.5 Monitoring

As phase I/II and pilot studies are not routinely reviewed by the Data and Safety Monitoring Board, it is the responsibility of the Team Safety Monitoring Committee (TSMC) to interpret toxicity data and make any decisions needed to protect subjects from undue risk. The TSMC will convene once a month to review monitoring reports. At a minimum the TSMC will consist of the protocol chair, the protocol vice chair, the DAIDS medical officer, the statisticians, the data manager, and the Network Community Advisory Board representative to the team.

In addition, toxicity summaries will be reviewed annually by the Study Monitoring Committee of the Translational Research and Drug Development (TRADD).

The safety and tolerability of the study medication will be monitored by means of adverse event reports (AER) and toxicity summaries presenting counts of subjects by Grade ≥ 3 laboratory and clinical events. It is required that these data be entered into the database within 3 business days of the time at which the results of the laboratory tests or clinical examinations become available. Toxicity summaries will be reviewed monthly via conference calls or by e-mail exchange. Subjects will be managed according to Section 7.0.

The data manager and statistician will also provide accrual reports (number of subjects accrued, number and percent discontinuing for any reason) and reports that identify subjects who meet the criterion for virologic failure. To facilitate sites in providing clarifications, SIDs will not be masked.

## 9.6 Analyses

9.6.1 Primary Objective

Primary objective: To estimate the first-phase viral decay rate in treatment-naïve subjects receiving RAL and FTC/TDF.

The primary analysis will be an AT analysis. Plasma HIV-1 RNA levels collected on days 0 to 56 will be used in parameter estimation except for (1) those collected after discontinuation, interruption, dose modification, or non-adherence to either RAL or FTC/TDF during days 0-14 (as determined from treatment records and adherence questionnaires), and (2) those at or after the first sign of rebound (defined as a rise of >0.30 log10 above the previous plasma HIV-1 RNA level). (For a given subject, HIV-1 RNA levels collected prior to such an event will be included in the analysis.)

Population and subject-specific decay parameters d1 and d2 from the bi-exponential model will be estimated by fitting a parametric nonlinear mixed-effects model to log10 plasma HIV-1 RNA levels.(4;5;10;45) Model-based 95% CIs around population estimates for d1 and d2 will be reported, and the distribution of subject-specific estimates will be summarized.

For any plasma specimen for which the HIV-1 RNA level is below the lower limit of detection (LLD) of the Ultrasensitive Roche Amplicor HIV-1 Monitor assay (50 copies/mL), a separate stored sample will be assayed for HIV-1 quantification using the single copy assay. In the event that any such single copy assay results are below the single copy assay LLD (1 copy/mL), to achieve unbiased estimates of d1 and d2 in the presence of censoring imposed by the assay lower LLD, an iterative multiple imputation procedure will be used.(5;45) This procedure is described in detail in the analysis plan.

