6.2.2 On-Study Evaluations

Entry (Week 0)

Entry evaluations must occur at least 48 hours after pre-entry evaluations and be completed prior to the initiation of study medications. Subjects must begin treatment on day 0 after study enrollment and after the entry evaluations have been completed.

Post-Entry

After entry, study visits up to day 7 must be scheduled within 1 day of the visit indicated in the schedule of events. Visits scheduled for days 10, 14, and 21 must be scheduled within 2 days, and for days 28 and 56 within 3 days, of the visit indicated in the schedule of events. All visits thereafter must be scheduled within 7 days of the visit indicated in the schedule of events.

Visit to Confirm a Suspected Virologic Failure

Subjects with a plasma HIV-1 RNA level ≥ 1000 copies/mL at or after 16 weeks and before 24 weeks, or ≥ 200 copies/mL at or after 24 weeks, will have a confirmatory plasma HIV-1 RNA test within 14 days after the initial plasma HIV-1 RNA sample indicating suspected virologic failure was obtained. Subjects who have their first detectable plasma HIV-1 RNA level at week 72 will not return for a confirmatory visit and will be considered treatment failures.

Subjects who have a confirmed virologic failure will report to the clinic to have the final visit evaluations performed and will be removed from the study.

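### The rebound rule in 9.6.1 acts on one unconfirmed rise of >0.30 log10, even between single-copy values, so noise can truncate adherent subjects and bias d2 upward; d1 is barely affected

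*Protocol*

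**What the plan says.** Section 9.6.1 defines the data for the primary as-treated fit: "Plasma HIV-1 RNA levels collected on days 0 to 56 will be used in parameter estimation except for" two groups of values. The first is values that follow an interruption or non-adherence during days 0-14. The second is "those at or after the first sign of rebound (defined as a rise of >0.30 log10 above the previous plasma HIV-1 RNA level"). What comes before is kept: "For a given subject, HIV-1 RNA levels collected prior to such an event will be included in the analysis".

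The same section brings low values into the series. For a specimen below 50 copies/mL, "a separate stored sample will be assayed for HIV-1 quantification using the single copy assay", with "single copy assay LLD (1 copy/mL") as the new floor. The rebound rule makes no exception for these values or for a change of assay between two visits.

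Section 9.4 restates the exclusion slightly differently: "Measurements obtained after treatment interruptions and/or rebound will be excluded". It adds, about the roughly 14% of A5166s subjects excluded for drug interruptions, that "HIV-1 RNA levels excluded for non-monotonicity were a subset of these".

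Section 6.2.2 sets the windows: "Visits scheduled for days 10, 14, and 21 must be scheduled within 2 days". Days 10 and 14 can therefore both fall on day 12.

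**The concern.** A rise between two successive measurements has two possible sources: a real change in viraemia, or noise. Once the first phase is over, the expected fall between neighbouring samples is small, and noise on two values can exceed it by 0.30 log10. The rule is one-sided. A chance low value stays, and the higher value after it goes, together with everything later. Deletion depends on the value that is deleted, so it is not ignorable and the mixed model does not correct for it. The retained second-phase points are selectively low, which makes the fitted second phase too steep.

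At stake are d2, a named secondary endpoint (9.2.2.2), and the first-to-second-phase transition time, which 9.6.2.2 derives from the fitted day 0-56 curves. Section 2.1 treats definition of the second and third phases as a critical secondary aim. Section 9.6.1 itself uses multiple imputation below the assay limit so that d1 and d2 are estimated without bias; the rebound rule works against that aim.

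**Working it through.** **The plan's own figures.** The protocol gives no trigger rate for this rule, no d2 and no measurement SD. Its d1 figures reproduce. With SD 0.20 and n = 30, SE = 0.20/√30 = 0.0365 and the half-width is 1.96 × 0.0365 = 0.07. The probability that the interval lies above 0.65 is Φ(0.15/0.0365 − 1.96) = Φ(2.15) = 98%. Those figures are not in dispute.

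**Inputs from the protocol.** Mean d1 0.80 and SD 0.20 (9.4); baseline RNA 10,000-300,000 copies/mL (3.0); samples on days 0, 2, 7, 10, 14, 21, 28 and 56 (6.1); switch to the single copy assay below 50 copies/mL, floor 1 copy/mL (9.6.1).

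**Assumptions.** Measurement SD 0.10-0.30 log10; d2 0.02-0.06/day; second phase 0.1-1% of baseline RNA; all subjects fully adherent with no true rebound; visits on nominal days.

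**Step 1: where the series is exposed.** By day 10 the first phase has fallen to exp(−0.80 × 10) = 0.03% of its starting level, so later samples are largely second phase. A rise from 10 to 21 copies/mL is log10(2.1) = 0.32 and triggers the rule.

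**Step 2: one interval by hand.** With d2 = 0.04/day, the expected fall over 7 days is 0.04 × 7/2.303 = 0.12 log10. A false trigger needs a noise difference above 0.30 + 0.12 = 0.42, and the SD of that difference is √2 × SD. The probability is 1 − Φ(0.42/(√2 × SD)): about 2% at SD 0.15, 7% at 0.20 and 12% at 0.25. The day 28 to day 56 interval is much safer. The expected fall is 0.49, the noise needed is 0.79, and the probability is about 0.3% at SD 0.20 and 3% at SD 0.30.

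**Step 3: whole series, by simulation.** Share of adherent subjects truncated over the full range of d2 and second-phase share:

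| SD (log10), both assays | Truncated | Of 30 subjects |
|---|---|---|
| 0.10 | 0-2% | 0-1 |
| 0.15 | 3-14% | 1-4 |
| 0.20 | 10-33% | 3-10 |
| 0.30 | 30-63% | 9-19 |

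With SD 0.20 on the standard assay and 0.30 on the single copy assay the share is 20-40%.

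**Step 4: effect on the estimates.** A nonlinear mixed-effects model was fitted to 60-70 simulated trials of 30 subjects per scenario, on all data and on truncated data. Population d2 rose, relative to the all-data fit, by 0-1% at SD 0.10-0.15 and by about 1-10% at SD 0.20. At SD 0.30 it rose by about 6% with d2 0.04/day and by 34% with d2 0.02/day. Mean d1 moved by about 0-2%, slightly downward (for example 0.785 to 0.776 at SD 0.20). The transition time was not simulated separately.

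**Step 5: confirmation by the next sample.** Second-phase share about 0.3%; a day 56 rise cannot be confirmed and is kept.

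| d2 (/day) | SD | Truncated: stated rule → confirmed | d2 shift: stated rule → confirmed |
|---|---|---|---|
| 0.04 | 0.15 | 6% → 0.3% | 1% → 0.1% |
| 0.04 | 0.20 | 18% → 2% | 3% → 0.6% |
| 0.04 | 0.30 | 45% → 9% | 6% → 1.3% |
| 0.02 | 0.20 | 28% → 5% | 10% → 2% |
| 0.02 | 0.30 | 57% → 16% | 34% → 5% |

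**The case against.** **The primary endpoint is safe.** This stands. d1 moves by about 0-2%. A reader might fear that a false trigger at an early day 2 visit leaves a subject with no data for d1. With mean d1 0.80, an assumed lag of 0.5 day and the two-sample baseline, the chance at nominal day 2 is at most 0.04% for SD up to 0.20. Even at day 1 it is 0.5% at SD 0.15 and 2.7% at SD 0.20.

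**The frequency is assumed.** This also stands. One might infer that many adherent subjects will be truncated, but that needs an SD the protocol does not give; at 0.10 the problem is negligible. The one piece of evidence in the document, the A5166s remark in 9.4, suggests few such cases there. It does not say which rule or assay floor A5166s used, so it neither clears the rule here nor shows that A5166s ignored rises without an interruption.

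**The rule is a safeguard.** Adherence is self-reported, and the first exclusion in 9.6.1 stops at day 14. A single-value rule catches later unreported lapses, and the simulation contains no true rebound against which to weigh that benefit. This is a real trade-off and the reason to keep the rule as a sensitivity analysis.

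**The contrast with virologic failure is weak.** Section 3.0 requires confirmation there, but confirmed failure takes a subject off study, whereas this rule only filters data. The point does not rest on the contrast.

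**Pooling.** The combined analysis with A5166s and A5160s in 9.6.2.1 uses the 9.6.1 restriction, so a new rule would alter that comparison. The fix allows for this.

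**Conclusion.** The point holds as a moderate one about the second phase. The rule needs no confirmation, has no copy floor, and deletes on the basis of the deleted value, so any bias it puts into d2 is upward. The transition time inherits the distortion through the fitted curves, by an amount not calculated here.

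The size depends on a measurement SD that the protocol does not state: from almost nothing at 0.10 log10 to a substantial loss of subjects from about 0.20, or if the single copy assay is the noisier one. The d2 shift is mostly below 10%. It is large only when high noise meets slow second-phase decay. The figures rest on the assumed ranges for d2 and second-phase share and on nominal visit days.

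The documents do not support reading this as a threat to the primary d1 estimate, or as proof that many adherent subjects will be lost.

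**What to change.** In 9.6.1:

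- Count a rise of >0.30 log10 as rebound only if the next sample in the day 0-56 series is also >0.30 log10 above the pre-rise value, or if the rise coincides with a recorded interruption or non-adherence.
- Do not apply the rule when both values are below 50 copies/mL.
- Keep an unconfirmed day 56 value. Waiting for week 12 RNA to confirm it would conflict with 9.1, which starts the analysis when the day 28 and 56 results are in.
- Report the single-value rule as a sensitivity analysis, and use it for the pooled comparison with A5166s and A5160s if those studies used it.
- Align 9.4, which excludes values after rebound, with 9.6.1, which also excludes the rebound value. The difference matters: if the triggering value were kept, deletion would depend only on retained values.

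The cost is a few lines of text and one extra model fit, with no new samples or visits. The downside is that a transient rise from unreported missed doses may stay in the main fit, and a day 28 rise can be confirmed only four weeks later. The sensitivity analysis shows how much either matters.

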9.6.2 Secondary Objectives

9.6.2.1 To compare first-phase viral decay rates for RAL and FTC/TDF to first-phase viral decay rates estimated for the superior arms of A5160s and A5166s.

Primary analysis: The Wilcoxon signed rank test will be used to compare subject-specific d1 estimates (obtained as above) to the value 0.67, which was the point estimate from d1 obtained on the (EFV-based) superior arm of ACTG viral dynamics substudy A5166s.

Secondary analyses:

1. In an AT analysis (i.e., restricting the data as described in 9.6.1), plasma HIV-1 RNA levels from A5248 will be combined with data from A5166s and A5160s.(10;45;46) The resulting subject-specific EBEs of d1 will be compared using the permutation-based Kruskal-Wallis test. (In a 2001 simulation study, compared to parametric tests, Ding and Wu conclude that permutation-based tests outperform likelihood-based tests [maintain type I error rate, and are robust to deviations from normality and small amounts of missing data].(9) In the majority of published viral-dynamics applications, the nonparametric Wilcoxon test is used for inference to compare d1’s among 2 groups.)
2. This nonparametric comparison of subject-specific EBEs will be repeated, with additional plasma HIV-1 RNA levels from A5248 subjects: plasma HIV-1 RNA levels obtained after discontinuation or modification of FTC/TDF, and/or after no more than 7 cumulative days of prescribed RAL doses are missed.

9.6.2.2 To estimate the second- and third-phase viral decay rates in treatment-naive subjects receiving RAL and FTC/TDF, and to estimate the times at which subjects' decay rates transition from first to second phase and from second to third phase.

Subject-specific second-phase decay rates will be estimated along with first-phase decay rates as described in 9.6.1 above. Similar estimation and inference procedures will be used to estimate third-phase decay rates, based on single copy assay results for plasma HIV-1 RNA samples obtained during weeks 24 to 72.(20;21) The primary analysis will be AT; a secondary analysis may be conducted wherein subjects who discontinued or interrupted the regimen are retained.

Times of transition from first to second phase and from second to third phase will be estimated using the methods of Bosch and colleagues(47) applied to subject-specific predicted log10 HIV-1 RNA from days 0-56 (first to second phase) and applied to log10 HIV-1 RNA.

9.6.2.3 To determine the proportion of subjects with plasma HIV-1 RNA below the limit of detection, <50 copies/mL, 24, 48, and 72 weeks after initiation of RAL and FTC/TDF.

The primary analysis will be an ITT analysis, wherein (1) if the study regimen (RAL and/or FTC/TDF) is modified or discontinued, the subject is retained in analyses, and (2) if a subject is lost to follow-up, the last observation is carried forward for subsequent time points. The proportion of subjects with plasma HIV-1 RNA <50 copies/mL at weeks 24, 48, and 72 will be reported along with the exact binomial 95% CI.

A secondary AT analysis will include only those subjects on the study regimen at the time of the evaluation.

9.6.2.4 To evaluate the safety and tolerability of the treatment with RAL and FTC/TDF.

Among subjects taking one or more doses of study drug, the proportion exhibiting each category of events will be reported, along with exact binomial 95% CI. Incidence rates, i.e., numbers of events per person-months of follow-up, will also be reported.

9.6.2.5 To evaluate changes in CD4+ T-cell counts 24, 48, and 72 weeks after initiation of RAL and FTC/TDF.

For the primary analysis, using the ITT approach described in 9.6.2.3, changes in CD4+ T-cell counts at weeks 24, 48, and 72 will be summarized descriptively via mean, SD, median, and quartiles. A secondary AT analysis may also be performed.

9.6.2.6 To investigate the occurrence of RAL and FTC/TDF-resistance mutations at virologic failure using very sensitive resistance assay techniques

Among subjects who took any dose of study drug, for each failing subject, the list of resistance mutations present at failure, if any, will be displayed. Of failing subjects, the proportion with specific mutations (ones occurring frequently among A5248 failures, ones known to be associated with RAL resistance) will be reported along with exact binomial 95% CIs.

9.6.2.7 To evaluate the relationship of RAL and FTC/TDF PK parameters with virologic and immunologic responses, including day 7 plasma HIV-1 RNA change from baseline and the magnitude and slope of changes in CD4+ T-cell counts over the first 14 days of study drug.

RAL, TDF, and FTC PK trough averages at steady state will be estimated.

9.6.2.8 To evaluate adherence by self-report in treatment-naïve subjects receiving RAL and FTC/TDF.

For each drug, visit and subject, the numbers and percent of missed doses will be calculated. Results will be summarized descriptively. Relationships between adherence to virologic response and to PK parameters may be investigated.

9.6.2.9 To investigate the decay rate in unintegrated proviral DNA in PBMCs.

The primary analysis will be of subjects as-treated, and will be descriptive. Trajectories over days 0-56 will be examined separately from trajectories over weeks 0, 12, 24, 48 and 72. Subject-specific trajectories of absolute quantities vs. time will be plotted (total cell-associated DNA and 3 subsets overlaid; subsets are LTR circular DNA and integrated proviral DNA as measured by an assay currently undergoing validation, and unintegrated linear proviral DNA calculated by subtraction). Medians (across subjects) at each time point will be plotted with corresponding 95% CIs. If subject-specific trajectories show similar shapes, specific features (e.g., slope for each subset, time at number of which LTR circles changes from increasing to decreasing) will be estimated and summarized.

9.6.2.10 To investigate longer-term viral decay in plasma, from single copy assay results obtained during weeks 24 to 72.

Primary analysis: For weeks 24 to 72, using the ITT approach described in 9.6.2.3, the proportion of subjects with plasma HIV-1 RNA below the limit of detection of the single copy assay will be reported, along with the exact 95% binomial CI.

9.6.2.11 To assess the magnitude and slope of changes in CD4+ T-cell count over the first 14 days of treatment with study drugs.

The primary analysis will be of subjects as-treated. Both day 14 changes in CD4+ T-cell count and slopes over days 0-14 will be summarized descriptively, and the linear association between these and first-phase viral decay rate estimates will be examined.

9.6.2.12 To examine the relationship between first phase virologic decay, immune activation in defined T-cell maturation subsets and CD4+ T-cell restoration.

The primary AT analysis will exclude endpoints corresponding to samples collected after an interruption or modification in the study regimen. The primary analysis will also include only those subjects for whom d1 could be estimated. Secondary analyses in which d1 is not a variable may include subjects without d1 estimates. Associations between the following pairs of variables will be examined, as described in the analysis plan: (1) baseline plasma HIV-1 RNA levels and baseline proportion of activated CM T-cells, (2) subject-specific d1 estimates and CD4+ T-cell increases (day 14, week 24; separate outcomes), (3) baseline CM T-cell turnover and CD4+ T-cell increases (day 14, week 24; separate outcomes), and (4) subject-specific d1 estimates and baseline CM T-cell turnover.

